### Recruitment {15}

All infants resident in the BHDSS or FWHDSS are eligible for enrolment in the PVS field trial. When infants present to immunisation clinics, trial staff confirm their identity and apply the trial inclusion and exclusion criteria. The mother/guardian of infants who meet the inclusion criteria and do not have exclusion criteria are informed about the nature of the trial as part of the informed consent process. The screening of infants and recruitment of participants is electronically entered in real-time into the trial data management system. A trial sticker is fixed to the child welfare card and the intervention schedule is marked on the child welfare card. Enrolment to receive the 1 + 1 intervention will cease 3 months prior to the close of clinical surveillance at the end of year 4 of the study.

Children aged 2 weeks to 59 months who are resident in the study area are under surveillance for clinical endpoints. Children who present unwell to health facilities in the study area are evaluated for criteria indicating the need for clinical investigation.

The cluster-wise selection of infants aged 6–12 weeks at the first dose of PCV13 for laboratory analysis of NP swabs will include all individuals in clusters with a number of individuals below a threshold number set for statistical efficiency. In clusters with numbers greater than the threshold, selection will follow a random scheme within each cluster. Patients will be randomly sampled within clusters from those born in the trial area, across age, time and space.

For the community surveys of pneumococcal carriage, residents of all ages will be included in the sampling frame. The HDSS will be used to determine cluster, village, and household population sizes and as a reference for the members of a household. Three-level cluster sampling using probability proportional to size will be used to select 2 villages within each of 68 clusters, with three households per village and 10 individuals per household. Ten individuals will be randomly selected from each household following the age-structure ratio 2:2:2:2:1:1 (0–11 months, 12–23 months, 2–5 years, 6–14 years, 15–44 years, 45 years and greater). Individuals not listed as resident within a selected household may be eligible if confirmed by the head of household as resident in the past 4 months.

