### Study setting {9}

PVS is being conducted in Upper and Central River Regions (URR and CRR) in the geographic area covered by the Basse and Fuladu West Health and Demographic Surveillance Systems (BHDSS and FWHDSS) (Fig. 1). The trial is based at the Basse Field Station of MRCG at LSHTM. The BHDSS population is 178,510 (225 villages) with 99,113 in the FWHDSS (213 villages); 19% of the population is aged < 5 years. The annual birth cohort in the trial area is around 10,000. The area has a child mortality rate of around 50 per 1000 live births. There are 68 geographically separate clusters of villages assigned to attend geographically separate EPI clinics (Fig. 2).

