### Outcomes {12}

The outcomes in the trial and the timing of their measurement are shown in Fig. 3. The primary trial endpoint is:
NP carriage of VT pneumococci in children aged 2 weeks–59 months with clinical pneumonia presenting to health facilities in the study area (measured in year 4).

Secondary endpoints will be:
NP carriage of non-vaccine type (NVT) pneumococci in children aged 2 weeks–59 months with clinical pneumonia presenting to health facilities in the study area (measured in year 4).Population-based and age-stratified NP carriage prevalence of VT and NVT pneumococci (measured in years 2 and 4).NP carriage of VT and NVT pneumococci in infants presenting for the first dose of PCV aged 6–12 weeks (measured in year 4).Incidence of radiological pneumonia in children aged 2 weeks–59 months (safety endpoint).Incidence of clinical pneumonia in children aged 2 weeks–59 months (safety endpoint).Incidence of clinical pneumonia associated with NP carriage of VT and NVT pneumococci in children aged 2 weeks–59 months (safety endpoint).Incidence of serotype-specific IPD in children aged 2 weeks–59 months (safety endpoint).Incidence of hospitalisation in children aged 2 weeks–59 months (safety endpoint).Mortality rate in children aged 2 weeks–59 months (safety endpoint).

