We have *a priori* interest to examine the following potential effect modifiers: (a) age (2–12 weeks, 13 weeks–9 months, 10–23 months and 24–59 months), (b) inpatient/outpatient status and c) severity (severe pneumonia defined as clinical pneumonia with O_2_ saturation < 92%). The number of cases of each endpoint in the subgroups above may not be sufficient to assess non-inferiority in those strata but may enable the detection of differences in effectiveness between groups. We will examine the strength of evidence for differences between subgroups using interaction tests.

A secondary exploratory measurement and analysis of the primary endpoint will be conducted in year 2 of the trial, in order to detect potential early development of superior impact in the 1 + 1 group. This secondary hypothesis is different to the primary hypothesis of non-inferiority and will use an alpha value of 0.05, as will the final analysis.

The secondary endpoints of community pneumococcal carriage will be measured in years 2 and 4 of the study while carriage in infants aged 6–12 weeks presenting for their first dose of PCV will be measured in year 4. Comparison of the two groups will be presented as a prevalence ratio (and 95% confidence intervals). The same analytical methods as the primary endpoint analysis will be used to account for cluster-level non-independence and the allocation of clusters. We will use the same non-inferiority measurement as the primary endpoint, where non-inferiority will be established if the upper-limit of the confidence interval around the prevalence ratio for VT carriage in the 1 + 1 versus 3 + 0 clusters is ≤1.38.

An exploratory analysis will be performed to measure the association between age-specific contact pattern frequencies and pneumococcal carriage. The association between physical and non-physical contact frequency and age-specific pneumococcal carriage will be analysed using GEE models.

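### The community survey samples by a fixed age quota but its stated model has no age term or standardisation, so a pooled all-age prevalence describes the quota mix and not the residents

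*Protocol article*

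**What the plan says.** The Recruitment section fixes the survey design. It will "select 2 villages within each of 68 clusters, with three households per village and 10 individuals per household", choosing individuals "following the age-structure ratio 2:2:2:2:1:1" across six bands: under 12 months, 12–23 months, 2–5 years, 6–14 years, 15–44 years, and 45 years or more. The Study setting section gives the population: "The BHDSS population is 178,510 (225 villages) with 99,113 in the FWHDSS (213 villages"), of whom "19% of the population is aged < 5 years", and "The annual birth cohort in the trial area is around 10,000".

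The Outcomes section defines the secondary endpoint as "Population-based and age-stratified NP carriage prevalence of VT and NVT pneumococci", measured in years 2 and 4. For its analysis, the Statistical methods section says "The same analytical methods as the primary endpoint analysis will be used to account for cluster-level non-independence" and for the allocation of clusters. The primary model in that section is a log-link binomial GEE with exchangeable correlation, adjusted for stratification variables. An age term is named for one endpoint only, carriage in infants aged 6–12 weeks. The survey's prevalence ratio is then tested against 1.38. The Sample size section gives power above 94% with 60 people in each of 68 clusters, 15% prevalence and an ICC of 0.02.

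**The concern.** An all-age sampling frame does not make a pooled estimate representative once people are drawn from it by age quota. Run as written, the community model averages over a sample in which young children are heavily over-represented. Carriage usually depends on age, and the Background names children aged 1–5 years as large contributors to transmission through high carriage. A pooled prevalence could therefore be reported as a population figure when it is not one, and this would happen even if the two schedules were identical.

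The ratio is a separate matter. The Objectives section expects schedule effects to act differently by age: adequate direct protection at 2–9 months and possibly better herd protection. If the ratio does vary by age, the pooled ratio weights the ages as the quota does.

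**Working it through.** **1. The stated power.** Design effect = 1 + 59 × 0.02 = 2.18. Effective n per arm = 34 × 60 / 2.18 = 936. Take 15% in both arms and one-sided 5%, as stated for the primary endpoint.
- Difference scale: margin 0.38 × 0.15 = 0.057; SE = √(2 × 0.15 × 0.85 / 936) = 0.0165; z = 3.45 − 1.645 = 1.81; power 96.5%. A standard two-proportion formula (15% against 20.7%) gives 94.3%. Both agree with the stated figure.
- Ratio scale: ln 1.38 = 0.322; SE = √(2 × 0.85 / (0.15 × 936)) = 0.110; z = 2.93 − 1.645 = 1.28; power 90%.

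Neither calculation allows for any loss from weighting.

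**2. Sample share against population share.** Quota: (2 + 2)/10 = 40% under 2 years. Population: 178,510 + 99,113 = 277,623. Under-2 share = 2 × 10,000 / 277,623 = 7.2%, or 6.8% after 5% child mortality; from the under-5 share, 19% × 2/5 = 7.6%. Children under 2 are over-sampled 5.3-fold (40/7.6) to 5.9-fold (40/6.8).

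**3. Pooled prevalence.** The article gives neither a full age structure nor age-specific carriage, so this step is an illustration. Assumed population shares for the six bands: 3.6, 3.6, 14.8, 25, 38, 15%. Quota shares: 20, 20, 20, 20, 10, 10%.

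| Assumed carriage by band (%) | Quota mix | Population | Quota / population |
|---|---|---|---|
| 15, 15, 15, 12, 8, 8 | 13.0% | 10.5% | 1.23 |
| 17, 17, 15, 8, 3, 3 | 12.0% | 7.0% | 1.71 |
| 20, 20, 15, 8, 2, 2 | 13.0% | 6.7% | 1.93 |

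First row: quota = 0.2 × (15 + 15 + 15 + 12) + 0.1 × (8 + 8) = 13.0. Population = 0.036 × 30 + 0.148 × 15 + 0.25 × 12 + 0.38 × 8 + 0.15 × 8 = 10.5.

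**4. Pooled ratio, same three profiles.**

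| Assumed ratio (1+1 to 3+0) | Quota ratio | Population ratio |
|---|---|---|
| 1.2 at every age | 1.20 | 1.20 |
| 1.5 in infants, 1.2 at 12–23 months, 1.0 above | 1.16–1.22 | 1.04–1.08 |
| 1.0 under 2 years, 1.2 at 2–5 years, 1.5 above | 1.12–1.20 | 1.29–1.39 |

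A constant ratio is not distorted. A varying one is, and the quota ratio can be the higher or the lower of the two.

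**5. Cost of weighting.** Kish factor = Σ(population share² / quota share) = 2 × 0.036²/0.2 + 0.148²/0.2 + 0.25²/0.2 + 0.38²/0.1 + 0.15²/0.1 = 2.10. Effective n per arm = 936 / 2.10 = about 445. At 15% prevalence:
- Difference scale: SE 0.0239; z = 0.057/0.0239 − 1.645 = 0.74; power 77%, against 96.5% unweighted.
- Ratio scale: SE 0.160; z = 0.322/0.160 − 1.645 = 0.37; power about 65%, against 90% unweighted.

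If the standardised prevalence is itself below 15%, as in step 3, power would be lower still.

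**The case against.** Weights are neither specified nor excluded. This is an article, a statistical analysis plan is to go to the steering committee, and survey weighting is commonly settled there. Selection uses probability proportional to size from HDSS counts, so the data for weights exist. This stands in part: it would be wrong to say that the protocol commits to an unweighted analysis. But the article does fix the model, names an age term for one other endpoint only, and gives a power figure that reproduces without any weighting loss.

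The endpoint is also age-stratified, and the quota serves that purpose well. Age-specific prevalences and ratios are not distorted by it. This stands, and over-sampling young children is not faulted here.

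A reader might infer that the quota biases the non-inferiority test, or that the decision against 1.38 would flip. The documents do not support that. Both arms use the same quota, and with a log link the pooled ratio equals the population ratio when the effect is constant across ages. A flip can be constructed by assuming benefit in the youngest and harm at older ages, but that runs against the article's herd-protection hypothesis. With excess carriage confined to children under 2, the quota ratio is the more conservative one.

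A reader might also infer that an inflated prevalence would enter the transmission model. The Justification of outcomes section describes age-dependent inputs, and nothing in it feeds in a pooled all-age figure.

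**Conclusion.** The point holds as one of specification and labelling on a secondary endpoint. The 40% and the roughly 7% follow from the article's own figures. Under the model as written, a pooled all-age prevalence is a quota-mix figure. It overstates resident prevalence if carriage falls with age: by 23% to 93% in relative terms under the assumed profiles, with the true size unknown because the article gives no age-specific carriage.

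The comparison between arms is internally fair. Its ratio differs from a population ratio only if the schedule effect varies by age, which the article makes plausible but does not show, and the direction could be either. The weighted power of roughly 65% to 77% rests on assumed age shares, a Kish approximation, 15% prevalence and a one-sided 5% level. The primary endpoint is untouched.

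**What to change.** In the Statistical methods section, for the community surveys:
1. Add the six age groups as covariates in the GEE tested against 1.38. This aligns the model with the sampling design. It does not by itself turn the tested ratio into a population ratio if effects vary by age.
2. Report arm-level all-age prevalence, and a supporting prevalence ratio, standardised to the HDSS age structure with village and household selection weights. Label any unweighted pooled figure as a quota-sample figure.
3. State that the 1.38 test and the power of over 94% refer to the age-adjusted ratio in the quota sample. Keeping the test there is reasonable: the margin was derived from carriage in children, and testing the weighted ratio would cost substantial power.

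The cost is wording and a modest amount of analysis, since the HDSS is already the survey's sampling reference. The downside is a wider interval for the standardised supporting estimate.

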## Assignment of interventions: allocation

### Sequence generation {16a}

Sixty-eight PVS trial clusters were randomised using a blocked scheme to ensure similar numbers of clusters were assigned to each group. Randomisation was stratified by a binary variable correlated with ‘high’ or ‘low’ cluster-level incidence of clinical pneumonia. Randomisation was carried out in permutations using the above stratification until selections achieved balance in terms of presence of a health centre and balance on population size between the two groups. In order to select the stratifying variable of cluster-level incidence of clinical pneumonia, cluster-level prevalence of ‘high’ or ‘low’ VT carriage in children with clinical pneumonia in the BHDSS was correlated with: clusterwise population density, rates of hospitalisation, clinical pneumonia, radiological pneumonia, IPD and mortality. Of the five listed outcomes, clinical pneumonia incidence had the closest correlation with VT carriage prevalence and thus was chosen as the stratifying variable.

### Concealment mechanism {16b}

A public event was held to announce group allocations of each cluster of villages in the PVS trial area. Representatives of each cluster were present at the public event. Selection of the randomisation list at the public event involved random selection of one of 100 valid randomisation lists. Thus, the investigators and cluster representatives had no knowledge of the allocation sequence at the time of group allocation.

### Implementation {16c}

An independent statistician prepared the cluster randomisation lists while trial staff and cluster representative were informed of the allocation as described in the previous section.

## Assignment of interventions: blinding

### Who will be blinded {17a}

Vaccinators and parents may be aware of the schedules used. Laboratory staff are blinded as specimens are labelled with a unique identification number that does not identify the study group. Blinding of laboratory staff will avoid bias given the laboratory-based measurement of the primary endpoint. Statisticians will analyse data in a pseudo-blinded fashion with the two groups identified by an indicator label rather than the identity of each group.

### Procedure for unblinding {17b}

Given that participants are not blinded to their group allocation, a procedure for unblinding is not needed.

## Data collection and management

### Plans for assessment and collection of outcomes {18a}

Resident children aged 0–59 months are under passive surveillance for clinical events. For all children presenting to a health facility in trial area staff provide standardised evaluation, investigation and recording of episodes in an electronic medical record. Data collection forms are not included in the protocol but are available on request.

Each child presenting unwell to a health facility in the trial area is registered, and if resident and aged 0-59 months, is eligible to be screened for clinical pneumonia. Whenever possible, a different staff registers attendance and conceals the infant welfare card from the staff performing clinical pneumonia screening (to minimise potential bias due to knowledge of the residential location and group allocation). Trial nursing staff screen for clinical pneumonia by determining if there is a history of cough or difficulty breathing, the respiratory rate, peripheral arterial oxygen saturation, and presence of lower-chest wall indrawing (Table 3).

**Table 3 Tab3:**
[figure not shown]
Clinical definitions for suspected pneumonia, septicaemia, and meningitis

Cough or difficulty breathing accompanied by one or more of the signs numbered 1, 2, and 3 is used to define clinical pneumonia at nurse screening

Cough or difficulty breathing accompanied by one or more of the signs numbered 1–8 is used to define suspected pneumonia as the surveillance diagnosis by nurses in outlying clinics and doctors in Basse and Bansang

*Raised respiratory rate for age is defined as greater than or equal to 60 breaths per minute for children less than 60 days of age, greater than or equal to 50 breaths per minute for children aged at least 2 months but less than 12 months, and as greater than or equal to 40 breaths per minute for children at least 12 months but less than 60 months. If the respiratory rate is raised on the first measurement it will be measured again after at least 5 min- and deemed raised if still greater than the given age-specific threshold

^‡^Impaired consciousness is defined as V, P, or U on the AVPU score, where A is if the patient is alert, V if responsive to verbal stimulus, P if responsive to pain stimulus, and U if unresponsive

^§^Prostration is defined as inability to feed or to remain in a seated position in a child otherwise able to do so

^||^Severe malnutrition is defined according to the WHO definition

Trial nursing staff use standardised criteria (Table 3) to classify patients according to a diagnosis of suspected pneumonia, septicaemia, and/or meningitis or other diagnoses consistent with the scheme of the Integrated Management Childhood Illness (IMCI) guideline. Patients are referred to clinicians in Basse and Bansang if there is suspected meningitis, hypoxia, or other severe illness requiring a higher level of care. According to standardised diagnosis patients are investigated as per the guideline in Table 4. Radiographs are performed in Basse, Bansang.

**Table 4 Tab4:** Guideline for investigation of patients

a. Patients admitted with any acute medical problem will have a blood culture taken, a plasma aliquot stored, a rapid malaria test done and haemoglobin measured. Samples will not be collected from children admitted electively or those with surgical problems, trauma, acute burns or non-infectious neonatal problems. b. Patients with suspected meningitis will have a lumbar puncture and chest X-ray done. c. Patients with clinical pneumonia will have a NP swab. If admitted to hospital with clinical or suspected pneumonia, patients will have a chest X-ray, NP swab and blood culture. d. Patients with suspected septicaemia without a focus will have a blood culture and chest X-ray done. e. Patients with suspected septicaemia with a focus will have a blood culture only. f. Lung aspirate will be considered if large peripheral consolidation is demonstrated by X-ray. g. Other investigations, including pleural aspiration, may be considered according to clinical indication.	

Fatoto and Jakhaly. Patients in Koina and Garawol are transported to Fatoto for X-ray and then returned for treatment. Patients in Gambisara and Demba Kunda are transported to Basse for X-ray. Patients in Janjanbureh are transported to Bansang for X-ray. Patients in Jakhaly are transported to Brikamaba for X-ray.

For resident patients with clinical pneumonia treated as an outpatient, or clinical or suspected pneumonia treated as an inpatient, a NP swab is taken (Table 4). We conduct frequent supervision of case ascertainment procedures and quality control of patient evaluation and NP swab technique. All children admitted are investigated according to the standardised guide in Table 4. Any child admitted with an acute medical problem has a blood culture taken, a plasma aliquot stored, a rapid malaria test done and haemoglobin measured. Samples are not collected from children admitted electively or those with surgical problems, trauma, acute burns or non- infectious neonatal problems. Participants admitted with suspected sepsis defined according to standardised criteria will have a blood culture done and those with suspected meningitis a blood culture and lumbar puncture. For those admitted with clinical pneumonia, or a danger sign, or focal chest signs, a blood culture and chest X-ray will be performed and pleural fluid or lung aspirate obtained as clinically indicated. Other investigations are done according to the clinical judgement of the attending clinician.

Radiological pneumonia is defined as radiological end-point consolidation as per the procedure for classification according to the WHO standard [49]. If multiple radiographs are taken during an episode of illness the worst radiographic appearance in the 3 days following the date of screening will be accepted as final. Pneumococcal pneumonia will be defined as a patient with clinical pneumonia accompanied by isolation of *S. pneumoniae* from a normally sterile site. Pneumococcal radiological pneumonia will be defined as WHO-defined end-point consolidation accompanied by isolation of *S. pneumoniae* from a normally sterile site. We will classify pneumococcal pneumonia as being caused by a) PCV13 vaccine serotypes or b) non-PCV13 vaccine serotypes. Non-typeable isolates will be included as a separate group. Episodes will be considered as separate events if the first and subsequent consultations are at least 30 days apart, or if a pneumococcus of a different serotype is isolated during each episode. Cases of pneumococcal pneumonia in which two different serotypes are isolated will be classified as one case of pneumococcal pneumonia, but two different episodes of serotype-specific IPD if the two different serotypes belonged to different serotype categories. Hypoxic pneumonia will be defined as clinical pneumonia with peripheral O_2_ saturation < 93%.

